### Patient reported outcome measures

Patients will complete online PROMs (Table 2), consisting of HRQOL questionnaires and symptom scores, and can see a graphical overview of their main results.

**Table 2 Tab2:** Patient reported outcome measures in the I-FILE study

	Description	Number of items and scoring	MCID	Reference
K-BILD	Self-completed health status questionnaire with 3 domains: breathlessness and activities, psychological, and chest symptoms	15 items Scores range from 0 to 100, with higher scores corresponding with better HRQOL	K-BILD total: 3.9 points	[30, 31]
L-PF	Questionnaire consists of 2 modules. The impacts module evaluates impact on daily activities. The symptom module evaluates shortness of breath, cough, and fatigue	44 items (Symptoms module: 23 items, Impacts module: 21 items) Scores range from 0 to 100, with higher scores indicating more impairment and lower HRQOL	L-PF Dyspnea: 6–7 points L-PF Cough: 4–5 points	[32, 33]
EQ-5D-5L	Questionnaire with 5 domains; mobility, self-care, usual activities, pain/discomfort, and anxiety/depression, combined with a VAS on health status with a scale from 0 to 100	6 items Higher score indicates better health status	EQ-5D-5L range: 0.0050–0.054 points EQ-VAS range: 0.5–5.0 points	[34, 35]
VAS	Symptom scores on cough, dyspnea, fatigue, and general wellbeing	1 item per symptom Scores range from 0 to 10, with higher scores on cough, dyspnea and fatigue reflecting more severe symptoms. Higher score on general wellbeing indicates better wellbeing	Not available	[19]
LCQ	Questionnaire on chronic cough	19 items The overall score ranges from 3 to 21, with a higher score indicating a better cough-related health status	1.3 points (IPF)	[36]
FAS	Self-administered questionnaire about fatigue	10 items The score ranges from 5 to 50 points, with a score of ≥ 22 points as cut-off for fatigue	4 points or 10% change (sarcoidosis)	[37, 38]
WPAI:GH	Questionnaire assessing impairment and productivity	6 items Outcomes are expressed as impairment percentages, with higher numbers indicating greater impairment and less productivity	Not available	[39]
GRoC	Global rating of change with regards to general well-being	1 item 15-point self-report scale (from − 7 to 7). Higher score indicates a better health condition compared to the previous study visit	5 points	[40]

*K-BILD* King’s brief Interstitial Lung Disease Health Status*, L-PF* the Living with Pulmonary Fibrosis*, EQ-5D-5L* The EuroQol five dimensions 5-level*, VAS* Visual Analogue Scale*, LCQ* Leicester Cough Questionnaire*, FAS* Fatigue Assessment Scale, *WPAI:GH* Work Productivity and Activity Impairment Questionnaire: General Health*, GRoC* The Global Rating of Change Scale

### Endpoints and statistical analysis

We will evaluate absolute changes in FVC (L and % predicted) measured with home spirometry, and oxygen saturation (%) measured with pulse oximetry, from baseline to 6, 12, and 24 months. These changes will be analyzed using a linear mixed model with disease and country as fixed effects. Repeated measurements within a patient will be corrected by random effects (intercepts or slopes, depending on the data). This model corrects for random missing data. Possible non-linear evolutions and correlations between subsequent observations will be accounted for through flexible modeling of the time variable and structured error terms in the variance–covariance matrix of the random effects. Absolute in-hospital FVC changes between baseline, 6, 12 and 24 months (L and %predicted), HRQOL, and symptom scores will also be assessed with linear mixed models. The correlation of home and hospital spirometry will be analyzed by calculating Pearson’s correlation coefficient, taking the individual mean FVC changes for each patient into account. Results will be used to optimize analytical methods to deal with outliers and missing data. Besides, a delta (Δ) change will be computed for HRQOL and symptom changes from baseline to 6, 12 and 24 months. Furthermore, we will use group based trajectory modeling and joint models to predict outcomes in individual patients (e.g. respiratory related and all cause hospitalizations, disease progression, and mortality) To measure time to decline in HRQOL, we will use the minimal clinically important difference (MCID) for all individual patient reported outcomes. Joint models will be used to assess time to reach the MCID. Adherence to the home monitoring program will be assessed by evaluating the completeness of data. The total number of measurements from each participant will be divided by the number of expected measurements, for pulmonary function as well as PROMs. The incidence rate of new oxygen prescription, non-elective hospitalization (respiratory and all cause), mortality (all cause and respiratory-related) will be summarized descriptively by diagnosis cohort. Disease progression will be defined according to the guideline criteria and its individual components, and will be compared with criteria used in different trials [16–18, 20]. We will also perform analyses with different cut-off values for FVC and DLCO. Multivariate logistic regression, ROC curve analysis and a multivariate Cox proportional hazards model will be used to identify possible predictive factors for disease progression and/or mortality. Differences between countries will be analyzed with ANOVA. If possible, HRQOL questionnaires will be validated for the different forms op PF by assessing internal consistency, discriminative ability, concurrent validity, and responsiveness. Patient and healthcare providers satisfaction with the home monitoring program will be summarized descriptively. An overview of the pre-specified endpoints is shown in Table 3.

**Table 3 Tab3:** Prespecified endpoints of the I-FILE study

*Primary endpoint*
Absolute FVC change measured with home spirometry from baseline to 6, 12 and 24 months (in % and L)
*Secondary endpoints*
Absolute FVC change measured with in-hospital spirometry between baseline and 6, 12 and 24 months (in % and L) Absolute DLCO change measured with in-hospital spirometry between baseline and 6, 12 and 24 months (in % and L) Change in oxygen saturation from baseline to 6, 12 and 24 months (in %) Correlations between home and hospital spirometry Adherence to daily and weekly home spirometry HRQOL and symptom changes between baseline, 6, 12 and 24 months Time to change in HRQOL Correlations between pulmonary function tests and PROMs at all time points Internal consistency, discriminative ability, concurrent validity, and responsiveness of PROMs in individual diseases Hospitalizations (all cause and respiratory related) Mortality Percentage of patients with disease progression Identification of markers for disease progression or death Percentage of patients with new oxygen prescription Differences in outcomes between countries Differences in outcomes between subgroups of PF Healthcare provider and patient satisfaction and experience with the online application

*FVC* Forced vital capacity, *HRQOL* Health related quality of life, *PROMs* Patient reported outcome measures, *PF* Pulmonary fibrosis

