### Study design and participants

The I-FILE study is an ongoing prospective multicenter, multinational, observational pilot study (NCT04304898). Patients with ILD, newly diagnosed in a multidisciplinary discussion (MDD), and PF on high-resolution computed tomography (HRCT), will be included in both community and tertiary centers in Belgium, France, Germany, Greece, the Netherlands, Norway and The United Kingdom. The trial is currently underway, and patients are being recruited. We aim to include approximately 700 patients in total. Patients will be considered newly diagnosed, when the diagnosis has been established within six months before inclusion in an MDD. In addition, patients should be either treatment naïve or have received treatment for their PF for a maximum of one month before inclusion. For more detail, inclusion—and exclusion criteria are shown in Table 1.

**Table 1 Tab1:** Inclusion and exclusion criteria of the I-FILE study

Inclusion criteria	Exclusion criteria
Newly diagnosed patients with ILD and PF on HRCT Pulmonary fibrosis present on HRCT according to current guidelines, confirmed by a thoracic radiologist at the MDD [20] MDD diagnosis ≤ 6 months before inclusion Treatment for ILD ≤ than 1 month	Not able to speak, read or write in the native language of the country where the patient is included
	Not able to comply to the study protocol, according to the judgement of the investigator and/or patient
	No access to the internet

*ILD* Interstitial lung disease*, PF* Pulmonary fibrosis*, MDD* Multi-disciplinary discussion*, HRCT* High-resolution computed tomography

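### No centre term is stated for the mixed model or the country ANOVA, so if outcomes correlate within centre, standard errors for country contrasts are too small

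*Protocol article*

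**What the plan says.** All of this is in the protocol article.

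- **Structure of the data** (Study design and participants). The study is an "ongoing prospective multicenter, multinational, observational pilot study". Patients "will be included in both community and tertiary centers in Belgium, France, Germany, Greece, the Netherlands, Norway and The United Kingdom". The recruitment aim is stated as "We aim to include approximately 700 patients in total". The number of centres is not given.
- **Mixed model** (Endpoints and statistical analysis). Changes in home FVC and oxygen saturation are analysed with a "linear mixed model with disease and country as fixed effects". On correlation, the text says "Repeated measurements within a patient will be corrected by random effects (intercepts or slopes, depending on the data"). In-hospital FVC, quality of life and symptom scores are also to be assessed with linear mixed models.
- **Country comparison** (same section). "Differences between countries will be analyzed with ANOVA". Neither the outcome scale, nor the unit of analysis, nor a centre or nesting term is stated for this test.
- **Role of the comparison.** Table 3 lists differences in outcomes between countries among the secondary endpoints. The Discussion presents possible differences in management and outcome across Europe as something the study will show.

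**The concern.** Every centre lies in one country, so country varies only between centres. The error term for a country contrast must therefore include the variation between centres within a country. A patient-level random effect does not supply it, and neither does the patient-level residual of an ordinary ANOVA. If two patients from the same centre resemble each other more than two patients from different centres of the same country, the stated analyses credit the country means with more information than they hold.

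The article gives reasons to expect some such resemblance. Patients are taught the spirometer by a member of the research team. Each centre's staff see a dashboard of their own patients and are told to contact those who repeatedly miss measurements. Only some hospitals have the platform inside their electronic patient file. Regular care is left as it is, and in-hospital lung function is part of the follow-up. Centre habits can thus enter measurement quality, adherence, hospital FVC and DLCO, and treatment.

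At stake is the country endpoint: differences between a few centres could be reported as differences between countries.

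**Working it through.** **Inputs from the article.** About 700 patients and seven countries. There is no figure of the plan's own to reproduce: it states no number of centres, no centre intraclass correlation (ICC) and no significance level or power for the country comparison.

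**Assumptions, for illustration only.** m = 10, 20 or 35 patients per centre, which means 700/10 = 70, 700/20 = 35 or 700/35 = 20 centres of equal size; centre ICC of 0, 0.01, 0.02 or 0.05; a nominal 5% level.

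**Formulas.**

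1. Design effect: DE = 1 + (m − 1) × ICC.
2. Ratio of the true to the reported standard error of a country mean or contrast: √DE.
3. False-positive rate of the seven-country test (7 − 1 = 6 degrees of freedom, 5% critical value 12.59): P(χ² with 6 df > 12.59/DE).

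**Two cells worked out.**

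- m = 10, ICC = 0.02: DE = 1 + 9 × 0.02 = 1.18; √1.18 = 1.09; 12.59/1.18 = 10.67; P = 0.099.
- m = 35, ICC = 0.05: DE = 1 + 34 × 0.05 = 2.70; √2.70 = 1.64; 12.59/2.70 = 4.66; P = 0.588.

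**Results.**

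| Patients per centre | ICC | DE | SE ratio | False-positive rate |
|---|---|---|---|---|
| any | 0 | 1.00 | 1.00 | 0.05 |
| 10 | 0.01 | 1.09 | 1.04 | 0.07 |
| 10 | 0.02 | 1.18 | 1.09 | 0.10 |
| 10 | 0.05 | 1.45 | 1.20 | 0.19 |
| 20 | 0.01 | 1.19 | 1.09 | 0.10 |
| 20 | 0.02 | 1.38 | 1.17 | 0.17 |
| 20 | 0.05 | 1.95 | 1.40 | 0.37 |
| 35 | 0.01 | 1.34 | 1.16 | 0.15 |
| 35 | 0.02 | 1.68 | 1.30 | 0.28 |
| 35 | 0.05 | 2.70 | 1.64 | 0.59 |

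**Check on the approximation.** The F test with 6 and 693 degrees of freedom was simulated with nested centres and 700/7 = 100 patients per country (400,000 draws). Ten centres of 10 per country with ICC 0.02 gave 0.098; five centres of 20 with ICC 0.05 gave 0.376; three centres of about 33 with ICC 0.05 gave 0.575. With ICC 0 the rate stayed at 0.05. With only two centres of 50 per country the rate was 0.206 at ICC 0.01 and 0.733 at ICC 0.05, so the upper end depends strongly on the unknown centre count.

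**The case against.** **The article is condensed.** One section covers the analysis of all endpoints, and a full protocol exists that is not shown. A centre term may be in it, and the article does not say that the ANOVA is one-way or on individual patients. That is fair, and it is why the point says that no centre term is stated and not that centre is excluded. But the article does not leave the method open. It names the fixed effects, the purpose of the random effects and the test for country, and an analyst who follows that text leaves centre out.

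**The inputs are assumed.** This also stands. With an ICC of 0 there is no error, and no table entry above that can be called the study's own error rate.

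**Centre correlation may be small for home FVC.** The main outcome is change within a patient, and a constant centre offset cancels in a change; only differences in slope between centres remain. The article also describes standardisation: a common application, spirometers of one maker, a baseline check against hospital FVC, a manual and videos, and hospital tests done to international guidelines. This argues for a low ICC in home FVC change. It does not make the ICC zero, and it says little about outcomes that depend on local care.

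**A reader might infer that the primary result is compromised, or that country standard errors are certainly too small.** The documents support neither. The effect falls on country contrasts, nothing shows harm to the pooled FVC change, and the direction holds only if the ICC is positive. Nor do the documents say that a significant country test leads to any decision; this is an observational pilot study with many secondary endpoints.

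**The remedy has limits.** With few centres, centre slopes may not be estimable in every model, least of all for oxygen saturation, which is measured only in patients with the oximetry device. A random centre effect widens intervals but does not adjust for the mix of community and tertiary centres. Where a country has a single centre, the two effects cannot be separated. These limits shape the fix, but none of them justifies an ANOVA that ignores centre.

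**Conclusion.** The point holds in conditional form. As written, the mixed model corrects only for repetition within a patient, and the country ANOVA has no stated centre term, although the design nests patients in centres and centres in countries. For any positive within-centre correlation, country standard errors are too small and the country test is anti-conservative.

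The size is not knowable from the article. Under the assumed range (10 to 35 patients per centre, ICC 0 to 0.05, equal centre sizes), the true standard error is 1.00 to 1.64 times the reported one and the false-positive rate is 5% to about 59%. These figures show sensitivity; they are not an estimate for this study. The consequence is confined to one secondary endpoint. A change of wording is worthwhile because it is cheap and the study was still recruiting when the article was written.

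**What to change.** - Replace the separate ANOVA by country contrasts (country-by-time) from the mixed model already planned, adjusted for disease. This also brings the country comparison under that model's handling of missing data.
- In that model, include centre within country as a random effect: an intercept, plus a slope over time where it can be estimated. Alternatively, use standard errors that are robust to clustering by centre. Either way, apply a small-sample correction, because the number of centres may be small.
- Report the number and type (community or tertiary) of centres per country.
- Where a country has only one centre, present its contrasts as descriptive.

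**Cost.** Only analysis wording changes; the one data item needed is each patient's centre. The downside is wider intervals for country differences.

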In current guidelines, disease progression is defined by a combination of worsening symptoms, radiological and/or physiological progression [20]. In-hospital forced vital capacity (FVC) trends are accepted as current standard to monitor physiological disease progression. Nevertheless, FVC measurements have an inherent variability and are usually measured at low frequency during visits to the pulmonologist, possibly delaying detection of disease progression, and consequently, management decisions. Online home monitoring, using eHealth technology, enables more frequent measurements of pulmonary function and symptoms by patients at home, which will help to get a more detailed overview of disease course in individual patients. Home monitoring in PF has gained increasing interest in recent years, with studies demonstrating its feasibility and reliability in this patient population, despite technical and analytical issues [18, 21–25]. Results of an international survey revealed that ILD healthcare providers are positive towards the use of online home monitoring for daily care, but also for research and registry purposes [26]. A large online multinational patient registry could be a major step towards the better understanding of PF heterogeneity, and thus improve its management. eHealth technology can help lift the burden of frequent data collection, and provide a more practical way of data collection. It could facilitate trans-border collaboration and pooling of data in a patient registry, as distances are bridged online.

In the I-FILE study, we aim to gain more insights in disease behavior and response to treatment in patients with PF using online home monitoring. In addition, we will evaluate the feasibility of a patient-led registry in PF.

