### Home spirometry and pulse oximetry

Home spirometry and oximetry measurements will be performed using a Bluetooth-enabled validated, CE-marked home spirometer (Spirobank Smart or Spirometer OXI MIR, Italy). Patients will be instructed by a trained member of the research team and will perform a minimum of three test blows on the home spirometer to ensure reliability of the home spirometry results. Home spirometry measurements will be considered reliable if the highest FVC value deviates less than ten percent from the in-hospital FVC value conducted at baseline, and if the difference between two consecutive measurements is less than 150 ml [28]. Patients are instructed to perform home spirometry approximately at the same time to reduce variability [29]. Oxygen saturation is measured in the subgroup of patients who use the Spirometer OXI, by placing their finger on the integrated sensor for 30 s. All measurements will be directly sent to the research team with a personal 5-digit code. Both patient and research team will have real-time access to the flow-volume loops, quality assessment of the measurements, and a trend line of the FVC and the FEV1 over time.

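### The only direct comparison of home with hospital spirometry is Pearson's correlation, which cannot quantify whether home readings over- or understate FVC decline; a paired difference with limits of agreement should be added.

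*Protocol article*

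**What the plan says.** The primary endpoint in Table 3 of the protocol article rests on the home device: "Absolute FVC change measured with home spirometry from baseline to 6, 12 and 24 months (in % and L"). The Background names the yardstick: "In-hospital forced vital capacity (FVC) trends are accepted as current standard to monitor physiological disease progression".

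Under Endpoints and statistical analysis, one sentence links the two methods: "The correlation of home and hospital spirometry will be analyzed by calculating Pearson’s correlation coefficient". Its closing clause describes what enters the calculation: "taking the individual mean FVC changes for each patient into account". Table 3 lists the matching secondary endpoint as "Correlations between home and hospital spirometry". The article states no paired difference, limits of agreement, concordance coefficient, or model with a device term.

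Two other passages bear on the point. The same section analyses hospital FVC separately, in its own mixed models for the changes to the same three time points. The section on home spirometry and pulse oximetry counts home readings as reliable "if the highest FVC value deviates less than ten percent from the in-hospital FVC value conducted at baseline", together with a repeatability condition.

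**The concern.** The primary result will be reported in litres and percent. Whoever reads it will want to know whether a home decline of a given size means the same decline on the hospital spirometer. That is a question of agreement. Correlation answers a different one: whether patients who decline more on one method also tend to decline more on the other.

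The two answers can diverge. If technique fades at home, so that every patient's home change is too negative by a similar amount, the ranking of patients and hence r are untouched. In addition, r rises with the spread of true change between patients. This cohort mixes diseases with very different courses, so a high r may owe more to heterogeneity than to closeness of the two methods.

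At stake is the interpretation of the primary endpoint, and of the uses that the Discussion hopes for at the level of the individual patient, such as early detection of progression.

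**Working it through.** The article gives no correlation or agreement figure to reproduce. The check is algebra, followed by an illustration whose variances are assumptions and not figures from the article.

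**Algebra.** Let X be the measured home change and Y the measured hospital change. For any constant a and any b > 0, corr(a + bX, Y) = corr(X, Y). This holds whatever the data. An offset in home *level* that is the same at baseline and follow-up cancels out of the change. The relevant a is an offset in the change itself.

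**Illustration 1.** Assumed: true change T with mean -200 mL and SD 300 mL (variance 90,000); independent errors with SD 100 mL per method (variance 10,000 each). Hospital change is Y = T + e₂, with variance 100,000.

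- *Home unbiased*, X = T + e₁: r = 90,000/100,000 = 0.90. Mean difference 0. Limits ±1.96·√(10,000 + 10,000) = ±277 mL.
- *Home decline overstated by 100 mL*, X = T - 100 + e₁: covariance and variances are unchanged, so r = 0.90. Mean difference -100 mL, limits ±277 mL around it.
- *True decline overstated by 50%*, X = 1.5T + e₁: var(X) = 2.25·90,000 + 10,000 = 212,500 and covariance = 135,000, so r = 135,000/√(212,500·100,000) = 0.926. Mean difference 0.5·(-200) = -100 mL. Limits ±1.96·√(0.25·90,000 + 20,000) = ±1.96·√42,500 = ±404 mL around it.
- *True decline halved*, X = 0.5T + e₁: var(X) = 0.25·90,000 + 10,000 = 32,500 and covariance = 45,000, so r = 45,000/√(32,500·100,000) = 0.789. Mean difference +100 mL, limits ±404 mL around it.

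In the last two cases only the true change is scaled and the error is not, so r does move. It moves up when decline is exaggerated and down when it is muted. If the *measured* change is scaled, error included, r stays at 0.90 exactly.

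**Illustration 2, other assumed values.** True change with mean -0.20 L and SD 0.25 L; error SD 0.10 L in hospital and 0.15 L at home. Then r = 0.0625/√(0.0725·0.085) = 0.796. A simulation of 200,000 pairs gave 0.796 in all six cases: unbiased, shifted by -0.10 L or +0.10 L, and measured home change multiplied by 0.5, 1.5 or 2. Mean home decline ran from 0.10 to 0.40 L against 0.20 L in hospital. The paired difference separates biased from unbiased: 0.00 L (limits -0.35 to 0.35) when unbiased, -0.10 L (-0.45 to 0.25) with a 0.10 L overstatement, and -0.20 L (-0.99 to 0.59) when doubled.

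**Precision of the proposed estimate.** The 95% CI half-width of the mean difference is 1.96·SD of the differences/√n. The article plans about 700 patients; 350 pairs stands for heavy loss.

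| Case | 700 pairs | 350 pairs |
|---|---|---|
| Illustration 1, unbiased or shifted | 277/√700 ≈ 10 mL | 277/√350 ≈ 15 mL |
| Illustration 1, true decline ×1.5 or ×0.5 | 404/√700 ≈ 15 mL | 404/√350 ≈ 22 mL |
| Illustration 2, unbiased or shifted | 13 mL | 19 mL |

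A 100 mL bias would be plain in every row.

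**The 10% check.** It is tied to the baseline hospital value, so it does not compare the two methods' change over two years. It is also wide: for an assumed hospital FVC of 2 to 3.5 L it allows 0.20 to 0.35 L.

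**The case against.** The strongest reply is that the plan is not blind to bias as a whole. Home and hospital FVC change are both modelled at 6, 12 and 24 months and both are listed in Table 3, so a mean home decline of 300 mL beside a hospital decline of 200 mL would be visible. This stands, and it limits the point to the direct comparison. Two separate estimates still give no confidence interval for their difference, which must account for both methods being measured in the same patients. They also say nothing about agreement within individuals.

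Other replies narrow the point further:

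- A reader might infer that the correlation will be offered as proof that the methods are interchangeable. The article does not say so. The use it names is improving the handling of outliers and missing data, and device agreement is not among the stated aims.
- A reader might infer that each patient is reduced to one value and the paired visits are lost. The phrase "taking the individual mean FVC changes for each patient into account" does not settle this. It may mean averaging home readings to obtain the change at each time point, and Table 3 speaks of correlations in the plural.
- A reader might infer that r misses every proportional bias. It does so when the measured change is rescaled. When only the true change is scaled, r shifts, as the 0.93 and 0.79 above show.
- This is one of many secondary endpoints in an observational pilot, and a fuller protocol exists. That lowers the weight of the point but does not remove it, because the article itself names both the statistic and the endpoint.

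**Conclusion.** The point holds for the direct comparison of the two methods. Pearson's r cannot quantify over- or understatement of decline on the home device. The invariance to offset and to rescaling of the measured change is exact and rests on no assumption. The sizes quoted (r of 0.90, 0.93 and 0.79; limits of ±277 and ±404 mL) depend on assumed variances and show only that r can stay still, rise or fall under a 100 mL mean bias.

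Nothing in the article shows that home spirometry is in fact biased, or that the primary analysis is invalid. The defect is a missing estimate. It is modest in weight because the group means will be reported anyway, but worth correcting because the primary endpoint is an absolute home change and the remedy is almost free.

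**What to change.** Keep Pearson's r as a descriptive measure. Add the mean paired home-minus-hospital difference, with its 95% CI and the 95% limits of agreement, for FVC at baseline and for the change from baseline to 6, 12 and 24 months. Average the home readings within a fixed window around each hospital visit, and set that window before the comparison is run. State in the text whether the correlated quantity is one mean change per patient or a change per time point.

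A joint mixed model of both methods with a device-by-time term is an optional alternative for the mean difference and copes better with visits where one reading is missing. It is not needed to repair the defect, and the correlation endpoint need not be replaced.

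The cost is analysis work and a few lines of text. The home and hospital measurements are already planned, so nothing is added for patients or sites.
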